#### Analysis of primary outcome

Mixed-effects model for repeated measure (MMRM) method is being used to analyse the primary outcome. The model assesses treatment group, visit, group and visit interaction, the randomisation variables of age, gender, ethnicity and hospital centre (three centres) as fixed effects; baseline AUDIT-C measure as a covariate; and participant as a random effect. The primary outcome is determined by the treatment effect at three months. Variance (co)variance structures are considered to model the within-subject errors, including, but not restricted to, unstructured, compound symmetry, autoregressive AR(1) structures. The Kenward-Roger method is being used to estimate the denominator degrees of freedom for fixed effects. Per Protocol analysis will be performed on the primary outcome as a sensitivity analysis. The per protocol population comprises all randomised participants excluding those who had protocol violations. When appropriate, post-hoc analyses will be conducted.

To assess the effectiveness of the programme for Māori and non-Māori, the analysis of the primary outcome will be repeated with the treatment and ethnicity (Māori vs non-Māori) interaction added to the model. As the study is not powered to test this interaction, the interpretation of this analysis will be made with caution.

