**Methods/design:**

Participants recruited to this single-blind randomised controlled trial comprised patients aged 16-69 years in three trauma-admitting hospitals in Auckland, New Zealand. Those who screened positive for moderately hazardous drinking were randomly assigned by computer to usual care (control group) or the intervention. The latter comprised 16 informational and motivational text messages delivered using an automated system over the four weeks following discharge. The primary outcome is the difference in mean AUDIT-C score between the intervention and control groups at 3 months, with the maintenance of the effect examined at 6 and 12 months follow-up. Secondary outcomes comprised the health and social impacts of heavy drinking ascertained through a web-survey at 12 months, and further injuries identified through probabilistic linkage to national databases on accident insurance, hospital discharges, and mortality. Research staff evaluating outcomes were blinded to allocation. Intention-to-treat analyses will include assessment of interactions based on ethnicity (Māori compared with non-Māori).

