### Sample size calculations

Based on the published literature on distribution in AUDIT-C scores in previous trials, we aimed to recruit approximately 570 participants to this study. This was based on a conservative estimate that 25% of patients screened will have AUDIT scores in the eligibility range for moderately hazardous drinking and a 75% participation rate. We anticipated that 400 (70%) of these participants would complete 12 months of follow-up. This sample size provides 80% power to detect a true difference of 7.5% (i.e., a mean difference between groups in AUDIT-C scores of 0.51) at the 0.05 level of significance.

As designed, this is a large trial relative to most alcohol intervention studies conducted previously. By recruiting patients from all major trauma-admitting hospitals in the greater Auckland region, we expected to recruit sufficient participants to determine effects on alcohol misuse and related harms (including injury recurrence) with adequate statistical power in a resource efficient manner.

The study also aimed to recruit as many Māori participants as possible with a minimum of 20% of the total sample, a situation deemed feasible given the ethnic distribution in the Auckland region. This sample size was expected to provide good power to test consistency in effect for Māori compared with non-Māori.

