### Statistical methods

Statistical analyses of the data gathered in this trial are being performed using SAS version 9.4 (SAS Institute Inc. Cary NC). All participants considered for eligibility for the study will be accounted for in analyses. The principal evaluations of interest in this study subscribe to the ‘intention to treat’ principle, i.e. all participants are analysed in the group to which they were randomised, regardless of whether they discontinued or deviated from the protocol. However, no outcome data were collected from participants who withdrew, beyond their withdrawal day.

This trial did not include plans for interim analyses or stopping guidelines. Accordingly, analyses are being performed after 12 month follow-up has been completed. Secondary outcome data regarding subsequent injury events are expected to require a minimum of 24 months to lapse from recruitment given the time required to get cause of death information in national mortality databases. Missing data are not imputed. All statistical tests are two-tailed with a 5% significance level maintained throughout the analyses.

A CONSORT trial profile will summarise the number of participants who were considered, fulfilled eligibility criteria, reasons for exclusions, randomised, withdrawn, and lost to follow-up. Data for the intervention and control groups are being summarised with respect to baseline demographic variables (age, sex, ethnic group), employment, education, mobile phone usage, cigarette smoking, recreational drug usage, self-reported role of alcohol in the injury, mechanism of injury, nature of injury, injury intent, baseline AUDIT, and AUDIT-C mean scores.

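### The primary repeated-measures model gives baseline AUDIT-C one slope for all visits, which can bias the 6- and 12-month contrasts if baseline-related loss differs between arms (minor, cheap to fix)

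*Protocol article*

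**What the plan says.** Under Analysis of primary outcome, the protocol article lists the model term by term: "The model assesses treatment group, visit, group and visit interaction, the randomisation variables of age, gender, ethnicity and hospital centre (three centres) as fixed effects", then "baseline AUDIT-C measure as a covariate", with participant as a random effect. The only interaction named in this model is group by visit. The within-subject covariance is left open, "including, but not restricted to, unstructured, compound symmetry, autoregressive AR(1) structures".

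The same section fixes the primary contrast: "The primary outcome is determined by the treatment effect at three months". The Abstract adds the later visits, "with the maintenance of the effect examined at 6 and 12 months follow-up", and the hypotheses also cover all three times.

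On attrition, Sample size calculations says "We anticipated that 400 (70%) of these participants would complete 12 months of follow-up", so about 30% are expected to be lost. Statistical methods says that missing data are not imputed and that nothing is collected after withdrawal.

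**The concern.** A single baseline covariate assumes that the baseline score predicts drinking equally well at every visit. That is doubtful here. The visits span 12 months, and the mode of collection changes: text message at 3 and 6 months, web survey or telephone at 12 months within the full 10-item AUDIT (Follow-up). If the true slope falls over time, a common slope adjusts too little at 3 months and too much at 12 months.

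This becomes bias only when the arms differ in baseline drinking among those still observed. The protocol describes a route by which they could:

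- Intervention participants receive 16 messages about their drinking; controls receive one neutral message.
- Participants are not blinded (Methodological limitations).
- A reply asking to stop ends all later texts (Screening of text-backs from participants). Read literally, this includes the texts that collect the 3- and 6-month outcome.

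If heavier drinkers leave the intervention arm more often, the ill-fitting slope turns the resulting baseline imbalance into an apparent treatment difference. At stake is mainly the question of whether the effect lasts.

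**Working it through.** **Inputs from the article.** 570 recruited, 400 completers (70%), 1:1 allocation, two-sided 5%, and "80% power to detect a true difference of 7.5% (i.e., a mean difference between groups in AUDIT-C scores of 0.51".

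**The plan's own figures.** 570 × 0.70 = 399, which agrees with 400. No SD is given, so the power cannot be checked independently. Solving back with 200 per arm: SD = 0.51 × √(200/2) / (1.96 + 0.84) ≈ 1.82. This value is used below.

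**Assumptions not in the article.** Baseline SD 1.5; residual correlation 0.5; unstructured covariance; retention 90/80/70% at 3/6/12 months (80/75/70% in the per-point runs in the fourth step); true baseline slopes as shown.

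**Mechanism.** Let βₜ be the true baseline slope at visit t, b the single fitted slope, and Δₜ the intervention-minus-control difference in mean baseline among those observed. Then roughly

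bias at visit t ≈ (βₜ − b) × Δₜ.

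There is no bias if Δₜ = 0 (same loss relation in both arms) or if βₜ is constant (then b = βₜ). With falling slopes, b lies between the first and last, so the biases at 3 and 12 months have opposite signs.

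**Large-sample check.** Maximum-likelihood fits to 400,000 simulated participants. Entries are the common-slope minus the visit-specific-slope contrast at 3/6/12 months. Odds ratios are for loss per baseline SD, control versus intervention; a negative contrast favours the intervention.

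| True slopes | OR 3 in both arms | OR 1 vs 1.5 | OR 1/1.5 vs 1.5 |
|---|---|---|---|
| 0.5/0.4/0.3 | 0.000/0.000/0.000 | −0.004/0.005/0.025 | −0.009/0.011/0.051 |
| 0.6/0.4/0.2 | 0.001/−0.001/−0.002 | −0.009/0.013/0.055 | −0.016/0.023/0.103 |
| 0.7/0.4/0.1 | 0.001/−0.001/−0.003 | −0.009/0.021/0.082 | −0.019/0.041/0.158 |

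The formula fits these. In the last row, OR 1 vs 1.5, Δ at 12 months was −0.18, so β − b = 0.082/(−0.18) ≈ −0.46 and b ≈ 0.56, between 0.1 and 0.7.

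**Stronger one-arm loss.** With slopes 0.6/0.45/0.3 and log-odds 0.4 to 0.7 per point in the intervention arm only, the 12-month bias is about 0.05 to 0.09 and the 3-month bias 0.02 to 0.03 in size. A second large-sample run gave 0.04 to 0.08 and 0.02 to 0.04. With slopes 0.8/0.4/0.1 and log-odds 0.7, the figures are about 0.23 and 0.06. Visit-specific slopes leave at most about 0.02, within simulation error.

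**Trial-size check** (N = 570, 1,500 replicates, slopes 0.7/0.4/0.1, Monte Carlo error about 0.004). With OR 1 vs 2, the common-slope bias was −0.011/0.033/0.127, against 0.005/−0.001/−0.004 with visit-specific slopes. With OR 2 in both arms, the common-slope bias was 0.002/0.006/0.000.

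**Precision at 3 months.** The variance ratio, common to specific, was 1.002 to 1.04, so the standard error is larger by √1.002 − 1 ≈ 0.1% to √1.04 − 1 ≈ 2% (0.5 to 2% in the per-point runs). Nominal 80% power becomes, at worst, Φ(2.80/√1.04 − 1.96) ≈ 78.4%, and at best 79.9%.

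**The case against.** The strongest case against has four parts.

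- **A main-effect baseline covariate is a standard, valid choice in a randomised trial, and the article is a condensed account.** A separate analysis plan may already contain the interaction. That is possible, but the article lists the model term by term and names one interaction, so the comment addresses a stated specification.
- **The bias needs a three-way condition that the article does not document.** This stands. A reader might infer that any drop-out related to baseline drinking biases the contrasts. It does not: with the same relation in both arms, even at an odds ratio of 3, the two models differ by at most 0.003. Nor does the article show that loss differed by arm; it gives only a route and an overall 70% completion.
- **The inputs are chosen and fairly demanding.** This also stands. Log-odds of 0.4 to 0.7 per point with SD 1.5 are odds ratios of exp(0.6) ≈ 1.8 to exp(1.05) ≈ 2.9 per SD in one arm and none in the other. Slopes of 0.8 to 0.1 mean a baseline correlation falling from 0.8 × 1.5/1.82 ≈ 0.66 to 0.1 × 1.5/1.82 ≈ 0.08. A change of mode does not by itself prove a change of slope.
- **Analysis was already under way when the article was written, so replacing the primary model is not free of post-hoc concerns.** This is right, and it shapes the fix.

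**Conclusion.** The point holds as a minor specification weakness. The stated model is restrictive, and the 6- and 12-month contrasts are unprotected if slopes change and baseline-related loss differs by arm. A 12-month bias of 0.05 to 0.09 is 0.05/0.51 ≈ 10% to 0.09/0.51 ≈ 18% of the design difference. Against a crude standard error of 1.82 × √(2/200) ≈ 0.18, it is at most about half a standard error. If heavier drinkers are lost from the intervention arm, the 3-month benefit is slightly inflated and the 12-month benefit shrunk, which would look like a fading effect.

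A reader might infer that the primary result is unsound or the trial materially underpowered. The documents do not support that: the 3-month bias is about 0.02 to 0.06 even under one-arm loss, and the power loss is at most about 1.6 points (80 − 78.4). All sizes depend on the assumed slopes, correlations and loss patterns.

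**What to change.** Add the baseline AUDIT-C by visit interaction to the primary mixed model and keep everything else. This costs one term, two degrees of freedom and no new data.

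Efficiency does not suffer if the slopes are equal. Only in an extreme scenario (odds ratio 1/3 versus 3, slopes 0.5/0.4/0.3) did the interaction cost visible precision at 12 months (standard error 0.176 against 0.173), and there it removed a bias of about 0.12.

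Because the article reports analysis of the primary outcome as under way, either date and document the change before unblinded results are used, or keep the stated model and report the extended one beside it as a sensitivity analysis for all three visits. A short table of mean baseline AUDIT-C among responders, by arm and visit, would show whether the condition for bias arose. If a separate analysis plan already has the term, no change of model is needed.

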#### Analysis of secondary outcomes

A range of self-reported measures of alcohol-related health and social outcomes, and experience with the study, will be evaluated. The difference between the intervention and control groups will be analysed using logistic regression models for binary outcomes adjusting for the randomisation variables of age, sex, hospital centre, ethnicity, and baseline AUDIT-C score.

Differences between the intervention and control groups with respect to time to subsequent injury events (ascertained through probabilistic linkage to national databases) will be evaluated using appropriate survival analytic approaches such as Cox proportional hazards models.

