## Methods/design

### Design and hypothesis

The YourCall™ study is a two-group, parallel, single-blind randomised controlled-trial. Individuals who screened positive for hazardous drinking (Alcohol Use Disorders Identification Test [AUDIT] score 7-15 for females, 8-15 for males) were individually randomised to an intervention group or a usual care group (control) in a 1:1 allocation ratio (Fig. 1). We hypothesise that in comparison to hazardous drinkers discharged following an injury admission who received usual care (control group), those who received a structured sequence of SMS-text messages (YourCall™) incorporating brief intervention from harm principles:

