### Participant recruitment and eligibility criteria

Participants to this study were recruited from November 8, 2012 to December 12, 2013, from one of the three trauma admitting hospitals (Middlemore, North Shore and Auckland City hospitals) in Auckland, New Zealand. The region includes urban, suburban and rural areas and has a population of approximately 1.4 million [36].

Trial eligibility criteria were (i) patients aged 16 to 69 years admitted to one of the three recruiting hospitals with an injury, (ii) screened positive for hazardous alcohol use (AUDIT score: 7-15 for females, 8-15 for males), (iii) used a mobile phone which is for their own use (i.e., not shared with another), (iv) were willing and able to read and send text messages, (v) were discharged home, (vi) were able to complete surveys in English, (vii) resided in New Zealand for the duration of the trial, and (viii) were competent and willing to provide informed consent to take part in the trial. Patients who were pregnant or whose injury was as a result of self-harm were excluded from this trial.

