### Outcomes

#### Primary outcome measures

The primary clinical outcome is the difference in hazardous alcohol use, assessed using the pre-validated AUDIT-C [38] tool (a shorter version of the AUDIT), between intervention and control groups at 3 months. The AUDIT-C is scored on a scale of 0–12 (scores of 0 reflect no alcohol use). In men, a score of 4 or more is considered positive for problem alcohol use; in women, a score of 3 or more is considered positive. Generally, the higher the AUDIT-C score, the more likely it is that the patient’s drinking is affecting their health and safety.

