### Trial procedures

#### Baseline data collection

Participants were recruited from patients admitted to one of the three recruiting hospitals for an injury-related cause. All those who were potentially eligible were given information (verbal and written) about the trial. If they were interested in participating, verbal consent was gained to determine eligibility (the form used ascertained the age, gender and ethnicity of respondents) and the initial screening undertaken i.e. alcohol drinker, mobile phone user, willing to receive and send SMS messages, able to complete questionnaires in English, not pregnant, and a New Zealand resident. Written informed consent was obtained from those meeting the eligibility criteria. These people were then screened using the AUDIT tool. Trained research assistants used *The straight up guide to standard drinks* brochure [37] to assist with the AUDIT tool questions. Participants screened as having non-hazardous drinking patterns (AUDIT score <7 for females, <8 for males) were excluded from randomisation. Participants with AUDIT scores >15 indicating possible alcohol dependence were also excluded from randomisation, provided with the number of the national Alcohol Helpline and the local community alcohol and drug services, and offered referral to that service.

Research assistants were present at the hospital every day of the week during regular working hours for the duration of the recruitment period to ensure participant enrolment was maximised. In addition, members of the clinical team informed potentially eligible patients that the study was taking place and that they may be contacted by one of the research team members. Trauma coordinators based at the three hospitals would also advise the research assistants if potentially eligible patients had been admitted. Hospital case-mix reports were generated on a regular basis as a method of double checking that all potential eligible patients had been approached.

Baseline data collected from study participants included: demographic details (age, gender, ethnicity), contact details (residential address, phone numbers, email address), mobile phone details and patterns of use, cigarette and drug use, the role of alcohol in this injury, and employment and education information. Participants were then given the choice of selecting one of the three language-based pathways through which the text messages are transmitted.

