#### Follow-up

Follow-up self-report surveys at 3 and 6, months using the AUDIT-C tool were conducted via text message. Three text-backs were required at 3 and 6 months follow-up. At the 9 month follow-up time point participants were asked via SMS messaging to text back to confirm their email address (which was provided at baseline). The total number of text-backs required was 7 text messages and participants were aware that they bear the cost involved. For participants on pre-pay plans this would cost a maximum of NZ$1.40. In order to acknowledge this cost and their participation in the study, treatment and control group participants receive a shopping voucher at the time of recruitment.

The 12-month web-based survey developed in LimeSurvey (open source software) included the full 10-item AUDIT as well as questions to gather self-reported data on health and social outcomes and legal consequences of heavy drinking during the follow-up period. Participants were asked two sets of ‘drinking consequences’ drawn from the GENACIS project (http://www.genacis.org/11) [39]. These comprised seven questions relating to possible alcohol-related ‘harms’ in the previous 12 months and seven questions relating to possible alcohol-related ‘troubles’. They were also asked questions about their alcohol-related healthcare service seeking behaviours, their current feeling about their readiness to change using a visual analogue scale [40], their experience with hangovers, and their experience of being in the study (i.e. the ‘good things’ about being in the study and what they ‘liked least’). Participants who were unable to complete the web-survey or preferred an alternative, had the survey administered by phone.

To encourage participants to reply to text message questions at the 3, 6, and 9 month follow-up points and to complete the online survey at 12 months, an incentive was offered. As part of the text message communication at each of the follow-up time points, participants were advised they would be eligible for a prize draw for a $200 supermarket voucher. Once each follow-up period had been completed for all participants, one participant was selected randomly from all those who had completed follow-up for that time-point. Four different participants each received a voucher.

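### Optional improvement: add baseline total AUDIT to the 12-month harm and trouble models, because AUDIT-C, their only baseline drinking covariate, is probably a weak predictor within the entry band

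*Protocol article*

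**What the plan says.** All references are to the protocol article.

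- **Entry.** Under Participant recruitment and eligibility criteria, patients must have "screened positive for hazardous alcohol use (AUDIT score: 7-15 for females, 8-15 for males". Baseline data collection confirms the upper limit: "Participants with AUDIT scores >15 indicating possible alcohol dependence were also excluded from randomisation".
- **AUDIT-C.** Primary outcome measures describes it as a shortened AUDIT and states: "The AUDIT-C is scored on a scale of 0–12".
- **12-month outcomes.** Under Follow-up, the web survey "included the full 10-item AUDIT as well as questions to gather self-reported data on health and social outcomes". These questions include "seven questions relating to possible alcohol-related ‘harms’ in the previous 12 months" and seven on troubles. The AUDIT in that survey is a follow-up measure and cannot serve as a baseline covariate.
- **Model.** Analysis of secondary outcomes specifies logistic regression for binary outcomes, "adjusting for the randomisation variables of age, sex, hospital centre, ethnicity, and baseline AUDIT-C score".
- **Baseline data held.** The full AUDIT is the screening test, so every randomised participant has one. Statistical methods lists among the summaries by arm "baseline AUDIT, and AUDIT-C mean scores".

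**The concern.** AUDIT-C is a natural covariate for the primary outcome, which is AUDIT-C itself. The same covariate is carried over to outcomes of a different kind, namely the consequences of drinking. The baseline items closest to those outcomes are the seven AUDIT items outside AUDIT-C.

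The entry rule sharpens this. Total AUDIT is AUDIT-C plus the remaining items, and the total is confined to a band. A man with AUDIT-C of 11 can have at most 15 - 11 = 4 other points. A man with AUDIT-C of 4 must have between 8 - 4 = 4 and 15 - 4 = 11. Among those enrolled, AUDIT-C therefore stands in poorly for baseline alcohol problems.

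At stake are some power for a stated secondary hypothesis and some protection against selective loss. The plan expects about 30% to be lost by 12 months and does not impute missing values, so only the model covariates can offset loss that depends on baseline problems.

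**Working it through.** **The plan's own figures.** The only calculated figures concern the primary outcome. 570 × 0.70 = 399, which agrees with 400 completers. 0.51 / 0.075 = 6.8 is the implied mean AUDIT-C. With "in a 1:1 allocation ratio", there are 200 per arm, and 80% power at two-sided 5% implies SD = 0.51 / [(1.960 + 0.842) × √(2/200)] = 0.51 / 0.280 = 1.82. These figures agree with each other. The article gives no harm or trouble rates, no power for these models, and no correlation between AUDIT-C and the other items. Everything below therefore rests on assumed distributions.

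**Why the band lowers the correlation.** Write C for AUDIT-C, P for the sum of the remaining items and T = C + P. There are seven remaining items if AUDIT-C is three of the ten, which fits the three text-backs at each text follow-up. Then

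Cov(C,P) = [Var(T) - Var(C) - Var(P)] / 2.

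Restricting T shrinks Var(T). The correlation becomes negative once Var(T) < Var(C) + Var(P), which depends on the spread of the parts.

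**Within-band correlation.** Rounded, range-limited normal scores were simulated and selected to T = 8 to 15 for everyone:

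| Assumed mean, SD of C; mean, SD of P | Latent r 0.3 | Latent r 0.5 | Latent r 0.7 |
|---|---|---|---|
| 5.5, 2.5; 3, 4 | -0.51 | -0.37 | -0.13 |
| 6, 2.5; 4, 5 | -0.56 | -0.44 | -0.22 |
| 5, 2.5; 2, 3 | -0.45 | -0.29 | -0.03 |
| 6.8, 1.82; 3, 3 | -0.29 | -0.12 | +0.13 |

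Before selection the correlations were +0.28 to +0.67. Inside the band, 11 of 12 are negative.

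Two cells can be checked by hand from the within-band SDs:
- First row, r 0.3 (SDs of C, P, T: 1.95, 2.40, 2.18): (4.75 - 3.80 - 5.76)/2 = -2.405, and -2.405/(1.95 × 2.40) = -0.51.
- Last row, r 0.7 (1.19, 1.66, 2.16): (4.67 - 1.42 - 2.76)/2 = 0.245. Dividing by 1.19 × 1.66 = 1.975 gives about +0.12, against +0.13 simulated from unrounded SDs.

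A second simulation with women entering at 7 gave -0.50 to +0.07, negative in 8 of 9 settings.

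**Prognostic value.** Assume log odds of harm rise by 0.25 per point of P and by 0, 0.125 or 0.25 per point of C. The explained share of latent variance is ρ² × V/(V + π²/3), where V is the variance of the linear predictor and ρ its correlation with the covariate. In the first row at r 0.3 with no effect of C:
- V = 0.25² × 2.40² = 0.36, and V/(V + 3.29) = 0.099 with both parts in the model.
- AUDIT-C alone: 0.51² × 0.099 = 0.026.

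Over all settings, AUDIT-C alone explains about 0 to 4%, total AUDIT alone about 3 to 9%, and both about 5 to 12%. The second simulation gave about 0 to 2% for AUDIT-C alone and 1.4 to 5.5% for both.

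**Power at 400 completers.** First row, r 0.5, assumed conditional odds ratio 0.55, 1,500 runs per setting (Monte Carlo error about 1 point):

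| Effect of C per point | No drinking covariate | AUDIT-C | Total AUDIT | AUDIT-C and rest |
|---|---|---|---|---|
| 0 | 75.7% | 75.7% | 77.7% | 77.7% |
| 0.125 | 75.9% | 76.1% | 77.5% | 77.8% |
| 0.25 | 75.3% | 75.1% | 78.2% | 78.1% |

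AUDIT-C changes power by at most 0.2 points. Going from AUDIT-C to both parts adds 2.0, 1.7 and 3.0 points. With no treatment effect, rejection rates were 4.3 to 6.3% over all adjustment sets (Monte Carlo error about 0.6 points), with no consistent difference between sets.

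**Selective loss.** A run with no treatment effect and 30% loss, with drop-out depending more strongly on P in one arm, gave odds ratios of 0.96 to 0.98 adjusting for AUDIT-C, and 0.997 to 1.02 with the remaining items added. Type I error stayed at 5.1 to 5.4%.

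**The case against.** The strongest reply is that the specified model is coherent, prespecified and valid. Under randomisation, leaving out a prognostic covariate does not invalidate the test, and the simulated error rates bear this out. One common covariate set across outcomes is a defensible choice, and tabulating baseline AUDIT by arm would reveal an imbalance. The gain is small and partly built in, since a simulation that gives the remaining items an effect must reward including them. All of this stands, and it is why the point is an improvement and not a fault.

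Three stronger readings are tempting, and the documents do not support them.

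- **That baseline adjustment as a whole is nearly worthless.** Age, sex, hospital centre and ethnicity are also in the models. The simulations omit them, so they say nothing about their value.
- **That higher AUDIT-C must go with fewer problem points among those enrolled.** The entry band fixes bounds, not a correlation. The band is 8 or 9 points wide, and with strongly correlated parts the within-band correlation is near zero or slightly positive.
- **That the treatment comparison is biased.** Nothing in the article says that loss is related to baseline problems. The 30% is an overall planning figure, and even the deliberately unfavourable run gave only a small distortion.

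It is also loose to call the gain one of precision. In logistic regression, an added prognostic covariate generally does not shrink the standard error. It moves the conditional log odds ratio away from zero. In the runs above, its mean went from -0.573, -0.569 and -0.575 with AUDIT-C to -0.606, -0.602 and -0.609 with both parts.

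**Conclusion.** The point holds as an optional improvement at almost no cost. The entry rule, the covariate list and the availability of baseline AUDIT are plain in the article. It follows from the algebra that the band lowers the correlation between AUDIT-C and the remaining items. That it becomes negative is likely but not certain (-0.56 to +0.13 under the assumptions tried). AUDIT-C alone is then probably a weak predictor of the harm, trouble and legal outcomes.

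The size is modest: about 2 to 3 points of power at 400 completers, with some protection if loss depends on baseline alcohol problems. The score distributions, outcome coefficients, harm rate and odds ratio of 0.55 are all assumed. The main runs use 8 to 15 for both sexes. The primary analysis is not affected.

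**What to change.** In the logistic models under Analysis of secondary outcomes, enter baseline total AUDIT beside baseline AUDIT-C and keep age, sex, hospital centre and ethnicity. Entering the sum of the remaining seven items instead is equivalent: with AUDIT-C in the model, it gives the same fit and the same treatment estimate.

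Timing matters. The article says that the allocation code is broken after the last follow-up visit, and that primary outcome analysis was under way while the last secondary data were being collected. If the 12-month comparison has not been unblinded, the change can be made to the main secondary models by a dated addition to the plan. If it has been, the specified models should stay as they are, with the extended model reported as a labelled sensitivity analysis.

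The cost is one degree of freedom in about 400 participants and a slightly different conditional odds ratio, which the report should state. No new data are needed, and no trial procedure changes.
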